### Methods in analysis to handle protocol non-adherence and any statistical methods to handle missing data

Multiple imputation methods are used to estimate missing data. The trial is supervised by the evaluation team, which is the contact for reporting of any adverse event.

#### Adverse event reporting and harms.

We expect no adverse events, as the interventions and assessment tools imply neither burden nor risks. However, in case of spontaneously reported adverse events like increased psychological burden, the families can contact the study team at any time and in case any adverse event is reported, it will be followed up and necessary steps will be taken.

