### Trial design and study setting and participant timeline

The present research project is designed as a one-group pre-post pilot study. As this trial is the first larger scale pilot trial on the feasibility and acceptability as well as the first trial on the preliminary efficacy of the app on sleep quality and the parent module, randomization, control groups, and blinding do not apply to the study design of this trial. The study is a single study conducted in the naturalistic setting of the app, meaning it was conducted exclusively in-app and within a German-speaking population. After consenting to participate in this study, the participants will be provided a 12-months free access to the Aumio app and receive the parent-centred email psychoeducation module at weekly intervals.

Once participants agree to the conditions of participation and meet the inclusion criteria, guardians are directed to the first assessment (T0). At T0, at the beginning of the intervention and before the first app use, data on sociodemographic characteristics and relevant covariates and the outcomes will be collected. After completing the first survey T0, participants are provided with free access to the Aumio app for one year and receive the parent-centred email psychoeducation module once a week. The intervention duration is set at twelve weeks. Six weeks after the intervention start and the first app use, the second measurement point (T1) takes place, where primary and secondary outcomes are assessed. Immediately following the conclusion of the 12-week intervention, the third measurement point (T2) is conducted, comparable to the T1 assessment (Fig 1).

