### Criteria for discontinuing or modifying allocated interventions

Participants can discontinue their use of the Aumio app, stop receiving the parent-centred email psychoeducation module, and consequently withdraw from the study at any time by uninstalling the app from their mobile devices and opting out of the email list. The intervention does not require contact with the study team.

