The acceptability of the Aumio app and the parent-centred email psychoeducation module will be assessed both quantitatively and qualitatively by examining the user’s satisfaction. The questions are derived from a study by Hiscock et al. [13], which examined the effects of a digital sleep intervention on child sleep and psychosocial outcomes of children and their caregivers. Satisfaction is assessed on 5-point Likert scale (1 = totally disagree/very unsatisfied, 5 = totally agree/very satisfied) generally and by specific factors, including satisfaction with the use of the product (“The app was easy to use”; “The e-mail course was understandable.”), the information provided (“The amount of information in the app was just right.”; “I was satisfied with the content provided by the app.”; “The amount of information in the e-mail course was just right.”; “I was pleased with the strategies the email course provided for my child’s sleep problem”; “I would have preferred to have a personal contact instead of the e-mail course to explain the strategies and their application.”), the feeling of safety (“I felt safe using the app.”; I felt safe participating in the email course.”), the subjective perception of improvement in the child’s sleep (“Using the app has helped my child to fall asleep.”; “Taking part in the e-mail course has helped my child to fall asleep better.”), and the intention to continue using the product in the future (“I would like to continue using the e-mail course in the future.; “I would like to use the app in the future.”). Likelyhood of recommendation to other parents (“How likely is it that you will recommend the Aumio app to other parents you know?”, “How likely is it that you will recommend the e-mail course to other parents you know?”) will be assessed using a 10-point Likert scale (1 = unlikely, 10 = highly likely). Quantitative data will be further supplemented by qualitative data on helpful content (“What has helped you and your child the most with the Aumio app?”, “What did you and your child find particularly helpful about the email course?”), ideas for improvement (“What would you change to improve the Aumio app?”, “What would you change to improve the email course?”), as well as moments when users experienced difficulty using the app (“When did you find it difficult to use the Aumio app?”). Additionally, we will assess changes in sleep duration (“Has your child’s sleep duration changed with the use of Aumio and the e-mail course?”) and whether parents sought advice from their local paediatrician regarding sleep problems (“While using the Aumio app and email course, did you contact your local paediatrician for more information on how to help your child sleep?”).

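### Adverse events are collected only through unprompted contact, so zero reports would put no upper limit on the event rate; one prompted item at T1 and T2 would

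*Protocol article*

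**What the plan says.** **Route for harms.** The adverse-event section of the protocol article opens with an expectation: "We expect no adverse events, as the interventions and assessment tools imply neither burden nor risks". It then gives the only stated route: "in case of spontaneously reported adverse events like increased psychological burden, the families can contact the study team at any time". Anything reported is to be followed up. The section on non-adherence and missing data names "the evaluation team, which is the contact for reporting of any adverse event".

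**Contact and withdrawal.** The section on discontinuing the intervention states: "The intervention does not require contact with the study team". Families withdraw by removing the app and unsubscribing from the e-mails. The section on concomitant and post-trial care gives every participant the study team's contact details. The consent and recruitment sections promise that no reason for leaving need be given.

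**Surveys.** After six weeks "the second measurement point (T1) takes place, where primary and secondary outcomes are assessed"; after twelve weeks "the third measurement point (T2) is conducted, comparable to the T1 assessment". The listed items cover satisfaction, perceived benefit, ideas for improvement, difficulty of use, a change in sleep duration and feeling safe ("I felt safe using the app", with a matching item for the e-mail course). One further item asks "did you contact your local paediatrician for more information on how to help your child sleep". The CSHQ, SI-KJ, KINDL and EBI are also completed.

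**Numbers.** The sample size section requires 196 families and inflates this to 456 for an expected dropout of 57%.

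**The concern.** Spontaneous reporting depends on a family deciding that something is an adverse event, linking it to the app or course, and writing to the team. A family that stops because the child or parent feels worse can leave without doing any of this. In the data it then looks the same as a family that lost interest. With more than half of the families expected to leave, this is not a marginal group.

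The surveys that could ask the question exist, but are not used for it. The items on effect are worded as help with falling asleep, so disagreement does not separate no effect from a worse state. The paediatrician item asks about seeking information, not about harm.

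Two things are at stake. The study is meant to inform a randomised trial, and a count of zero without a known reporting share is an unreliable input to it. The promise to follow up every reported event also works only for events that the team learns of.

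**Working it through.** **The plan's own figures.** 196 / (1 − 0.57) = 196 / 0.43 = 455.8, rounded up to 456. This reproduces, and 456 − 196 = 260 families are expected to be lost. The document gives no figure on adverse events.

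**Inputs.**
- Families enrolled: 456 (sample size section).
- Families expected to remain: 196 (same section), taken here as the T2 responders.
- Share *s* of events reported unprompted: not in the document. Values of 0.05 to 0.50 are assumed to show the range.
- True event rate *r*: not in the document. Values of 1% and 2% are used as examples.
- Families are treated as independent, with the same *s* for all.

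**Upper limit after zero events.** The one-sided 95% limit is 1 − 0.05^(1/n).
- n = 456: 1 − 0.05^(1/456) = 0.65%.
- n = 196: 1 − 0.05^(1/196) = 1.5%.

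These limits apply to the *reported* rate, *r* × *s*. The limit for *r* is the same value divided by *s*.

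| Assumed reporting share | Limit for the true rate, 0 of 456 |
|---|---|
| 100% | 0.65% |
| 50% | 1.3% |
| 25% | 2.6% |
| 10% | 6.5% |
| 5% | 13% |

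As *s* is unknown under the stated method, no row can be chosen and no limit can be quoted.

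**Chance of hearing nothing when events occur.** P(0 reports) = (1 − *r* × *s*)^456.
- *r* = 2% (0.02 × 456 = about 9 families), *s* = 10%: (1 − 0.002)^456 = 40%.
- *r* = 2%, *s* = 5%: (1 − 0.001)^456 = 63%.
- *r* = 1% (about 5 families), *s* = 10%: (1 − 0.001)^456 = 63%.
- *r* = 2%, *s* = 50%: (1 − 0.01)^456 = 1%.

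With low unprompted reporting, an empty record is therefore quite compatible with several affected families. With reporting of one half or more it is not, at a rate of 2%.

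**What a prompted item adds.** Zero positive answers among 196 responders give a limit of 1.5% without an assumed unprompted share, provided that responders disclose events when asked. The limit says nothing about the 260 families expected to be lost.

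**The case against.** The case for leaving the plan as it is has substance.

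- **A contact route exists.** All families receive the team's details and may write at any time. A reader might infer from "The intervention does not require contact with the study team" that the trial allows no contact. The text says only that contact is not required.
- **The trial measures the plausible harms.** Worse sleep, lower well-being and more parental burden would move the CSHQ, SI-KJ, KINDL and EBI scores. The sleep-duration item is neutral in direction, and the safety ratings can be answered negatively. A reader might conclude that the trial would show nothing about harm; that goes too far, because it holds for the adverse-event count and not for the trial.
- **Zero events do not enter the primary conclusion.** Feasibility is defined by users, dropout, usage and recruitment, and acceptability by satisfaction. A reader might infer that an empty adverse-event record would support feasibility or acceptability. The definitions do not support this, and nowhere is zero said to mean safe.
- **The expectation of no events does not contradict the example that follows it.** Naming increased psychological burden is a contingency after an expectation.
- **A survey item does not reach everyone.** Surveys are planned for all, but dropout is expected to be 57%, and those who leave may be those affected.

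These points narrow the concern without removing it. Availability of a contact does not make the reporting share known. The indirect measures are planned as descriptive summaries and repeated measures ANOVA, and the confidentiality section says that data are evaluated only as a whole. None of them is designated as harms data or used to identify an individual event. The limited reach of the surveys is a reason to state whom the limit covers, not a reason to leave the question out.

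**Conclusion.** The point holds in this form: the stated collection method is unprompted contact only, and a count of zero from it gives no upper limit on the event rate and must not be read as absence of harm. This is a weakness in a method that the article itself fixes, not a detail left to a fuller plan.

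The size depends on an unknown. The limit of 0.65% needs complete reporting; the range of about 1.3% to 13% rests entirely on the assumed reporting shares of 50% to 5%, for which the document has no figure. That the count will in fact be near zero is a fair inference from the sponsor's expectation and the passive route, not a stated result.

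The consequence is limited to what can be said about harms and passed on to the randomised trial. The feasibility, acceptability and efficacy analyses are not affected. The change is worth making because it is specific and cheap.

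**What to change.** 1. Add one fixed item to T1 and T2: whether, since the start, the child's or the parent's well-being or sleep has become worse or the app or course has had any unwanted effect. Record yes or no, what, when, and whether it led to stopping.
2. Route every yes to the evaluation team already named as the contact. The confidentiality section should say how this works with pseudonymous survey data.
3. Add a reason field at e-mail opt-out and mark it as optional, so that it agrees with the promise of withdrawal without giving reasons.
4. Report prompted events with the number asked and the number answering, separately from spontaneous reports. State that any limit from prompted answers covers responders only (1.5% for 0 of 196), and that an absence of spontaneous reports is not evidence of absence of harm.

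The cost is one survey item at two time points, a notification in the existing survey platform, a field on the opt-out page and a notice to the ethics committee. Design, sample size and app functions stay as they are. The downside is that some non-specific complaints will be recorded that cannot be attributed without a control group. Families who leave and do not answer remain unobserved.

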#### Frequency and plans for auditing trial conduct.

No audits are planned

#### Plans for communicating important protocol amendments to relevant parties.

Any deviations from or changes to the protocol will be documented. Significant changes will be reported to the Ethics Committee of the Freie Universität Berlin and documented in the German Clinical Trials Registry.

#### Dissemination plans.

The results of the study will be submitted for publication in relevant journals and on the Aumio website.

## Discussion

The aim of the present pilot study is to test the feasibility, acceptability and preliminary efficacy of a German-language audio-based app for improving child sleep quality in combination with a parent-centred email psychoeducation module. Results will inform a future randomized-controlled clinical trial and for future modifications of the interventions. The significance of the present study lies in the pressing need for research in the field of mhealth interventions targeting child sleeping problems. While there are a high number of apps available that claim to help children in falling asleep and improving their sleep, most only offer white noise or soothing music and do not specifically address sleep habits [35]. Moreover, there is a scarcity of evidence-based and app-based interventions for children in general. Many apps promote improved sleep onset, well-being, and sleep habit development without incorporating evidence-based behavioural strategies [35]. Filling this gap using a large sample is a strength of the present study.

A limitation of the study design is the way in which the secondary user-centred objectives are collected. These are exclusively collected retrospectively in the third-party report by one parent. In particular, children’s sleep quality is not recorded in self-report. This approach may overlook potential cases of sleep problems in children, as highlighted by Paavonen et al. [36], who suggest that one-third of such cases may go undetected if only parents are surveyed. Therefore, it would have been beneficial to include both children’s and guardians’ perspectives in assessing children’s sleep. Due to the target group of children aged 6–12 years, sufficient reading skills are not to be expected in a comparatively large number of cases until the age of 7 or 8 years. Another limitation is the use of subjective, parent reported methods for assessing children’s sleep, without incorporating objective measures. Subjective methods for data collection depend on self-reported information and may be influenced by biases or inaccuracies [37]. Objective methods that directly measure sleep and recovery function and thus provide indirect information about sleep quality were not used [37]. In particular, discrepancies in the recording of total sleep time and wake after sleep onset have been reported in several studies [38]. This inconsistency must be considered when interpreting the data and highlight the need for a comprehensive approach that combines subjective and objective measures to obtain a more accurate understanding of sleep. Future studies should consider incorporating children’s self-report and guardians report as well as objective measures of sleep to provide a more comprehensive assessment of sleep quality.

Lastly regarding the analysis of the preliminary efficacy, the study design of the present research project, the single-group pre-post design, must be considered critically in itself. The methodological weaknesses were summarised by Maier-Riehle and Zwingmann [39]. First, the effect sizes cannot be interpreted causally because the observed changes are not exclusively attributed to the intervention but also to other confounding causes. In addition, different calculation methods are proposed for determining effect sizes in the single-group pre-post design. As a result, effect sizes are not comparable among each other and lead to different patterns of results. Last, it should be noted that Cohen’s limits of interpretation cannot be invoked when interpreting effect sizes, as these are based on independent samples and provide an overly optimistic measure in designs without a control group. No alternative limit of interpretation for effect sizes in single-group pre-post designs has been established at this time [39]. Nevertheless, the inclusion of covariates which possibly influence the primary and secondary outcomes aims to provide a more detailed picture of the preliminary efficacy of the Aumio app and can further prepare a larger, RCT with the focus on testing the efficacy of the Aumio app.

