### Objectives

The aim of this pilot study is to test the feasibility, acceptability and preliminary efficacy of the Aumio app and the parent-centred email psychoeducation module. We aimed (1) to examine the feasibility and acceptability of the of the Aumio app and the parent-centred email psychoeducation module. We therefore aimed to conduct qualitative and quantitative data to gain comprehensive insights. In addition, we also aimed (2) to collect information for improvements of the Aumio app and the parent-centred email psychoeducation module from a user’s perspective. We furthermore aimed (3) to examine the preliminary efficacy of the Aumio app and the parent-centred email psychoeducation module. As secondary user-centred outcomes, we aimed to examine whether its use improves children’s sleep, covering a broad range of facets to adequately capture the multidimensional nature of sleep. Furthermore, preliminary efficacy on child’s health-related quality of life and effects on parental stress will be tested as secondary user-centred outcomes. In order to further improve the feasibility and to synthesize recommendations for use, it will be investigated (4) at which intensity of usage the Aumio app significantly affects the feasibility and satisfaction as well as the secondary user-centred outcomes. The intensity of usage will be analysed continuously as well as divided into 4 levels (12, 18, 24, and 30 uses during the study period) and included in the analyses.

The primary, feasibility hypothesis refers to the user’s subjective perspective on the Aumio app and the parent-centred email psychoeducation module, with the assessment time points 6 weeks after the start of the app use, at the midpoint of the 12-week parent-centred email psychoeducation module and again another 6 weeks after. We hypothesize that the Aumio app and the parent-centred email psychoeducation module is feasible. We also hypothesize Aumio app and the parent-centred email psychoeducation module is accepted among the users. We further hypothesize that the present study design is feasible to conduct a large scale trial on the effectiveness.

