The secondary, user-centred hypothesis refer to comparisons of endpoint scores pre app use, at the same time points as the feasibility survey. We hypothesize that 6 weeks and 12 weeks after the start of the app use, children’s sleep quality will be significantly increased (secondary, child-centred endpoint) and health-related quality of life will be significantly higher (secondary, child-centred endpoint). Furthermore, we hypothesize that parenting stress will be significantly reduced 12 weeks after the start of the use of the email psychoeducational program (secondary, parent-centred endpoint). Exploratory analyses will also be conducted to determine to what extent usage behavior influences the effects on primary and secondary outcomes.

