### Intervention description

The intervention consists of two components: the Aumio app and the parent-centred email psychoeducation module. Both are made available to participants. Aumio is a smartphone application designed to provide easily accessible health interventions for children and to promote healthy sleep and strengthen children’s mental health. It focuses on children’s sleep, relaxation, concentration and emotions. In the sleep module, Aumio offers a variety of audio stories, fantasy journeys and sounds for falling asleep to make going to bed in the evening as relaxing as possible for children. In addition, psychoeducation and the playful learning of relaxation techniques by means of meditations and dream journeys are integrated into the Aumio app. The meditation techniques are taught in a child-friendly way and made easily accessible for children. The exercises and stories are based on cognitive-behavioral techniques such as autogenic training or progressive muscle relaxation. The meditations and dream journeys for falling asleep have a duration between 5 and 20 minutes. In the intervention, families are advised to use the Aumio app at least twice a week in the evening, before bedtime. However, participants are encouraged to integrate the Aumio app into their daily routine in a manner that is suitable for them.

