In addition, the parent-centred email psychoeducation module accompanies the use of the Aumio app and is emailed to the guardians once a week. The course addresses various aspects of children’s sleep to provide guardians with an understanding of child sleep and associated challenges. Each week focuses on a specific topic that covers relevant aspects of children’s sleep and sleep habits. First, the importance of good sleep quality for child development is discussed. Then, falling asleep is addressed by teaching the creation and establishment of bedtime routines and highlighting the importance of a comfortable sleep environment. Potential obstacles are also addressed. The parents are also taught how to help their children fall asleep on their own and how to make the process of accompanying their child to sleep less stressful. The course then tackles issues with staying asleep and provides strategies to support the child in falling back asleep after a nighttime awakening. Last, the course discusses how the child’s daytime activities can influence their sleep. For each topic, practical tips for implementing the concepts in daily life are provided alongside the theoretical explanations. The knowledge learned can be tested weekly in a small quiz in the Aumio app. In addition, the most important content is compiled in a child-friendly way and sent as a playfully designed info sheet as an attachment to the e-mail.

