### Sample size

With regard to the required sample size, two factors were considered in the present study: The Aumio app for the children and the parent training. For the parent training, we first considered effects on child outcomes as a basis for sample size calculation. An average effect size of parent training of d = 0.20 was found in a meta-analysis on the effectiveness of family-based prevention interventions [31]. An average effect size of d = 0.21 of universal prevention programs was found in a meta-analysis on German-language effectiveness research [32]. Based on these findings, with an assumed power of.90, an alpha error level of.05, and an effect size of.21, a required sample size of 196 was calculated using the software g*Power [33].

Considering the drop-out rate (DOR) observed in the unpublished master’s theses on the Aumio app, this was also considered for sample calculation. In one of the most recent master’s theses on the effectiveness of the Aumio app, a drop out of 57.14% was found in the treatment group. Based on an expected DOR of 0.57, the number of cases is multiplied by the correction factor 1/(1-DOR) [34]. If the previously calculated sample size is increased by the expected DOR, a final required sample size of 456 is needed.

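### The app and the parent e-mail course reach every family together, so changes and usage associations should be reported for the combined package, not as effects of the app

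*Protocol article*

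**What the plan says.** The Intervention description defines one package for everyone: "The intervention consists of two components: the Aumio app and the parent-centred email psychoeducation module. Both are made available to participants". The section on trial design confirms joint delivery after T0, when "participants are provided with free access to the Aumio app for one year and receive the parent-centred email psychoeducation module once a week". It also says that "randomization, control groups, and blinding do not apply to the study design of this trial", so no group receives only one component.

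The wording of the efficacy aims varies:

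- **Joint wording.** Aim 3 under Objectives and the opening of the Discussion name the app and the course together.
- **App wording.** The last paragraph of the Introduction puts sleep quality, quality of life and parental stress under efficacy of the app, and mentions the course only as applied alongside. Objective 4 asks "at which intensity of usage the Aumio app significantly affects the feasibility and satisfaction as well as the secondary user-centred outcomes", in order to derive recommendations for use. The section on statistical methods names app usage, continuous and in four levels (for example 12, 18, 24 and 30 uses), as the exposure. The last limitations paragraph of the Discussion says that including covariates "aims to provide a more detailed picture of the preliminary efficacy of the Aumio app and can further prepare a larger, RCT".

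**The concern.** A reader of the results will want to know whether the app improves children's sleep. This design can describe what happens to families who have both components. It cannot say which one was responsible. The issue is not academic, because the course aims at the same target: according to the Intervention description it covers bedtime routines, the sleep environment, falling asleep alone and night waking.

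Two outputs depend on the attribution. One is the recommendation on how often to use the app, which objective 4 is meant to supply. The other is the case for a later randomised trial centred on the app. If part or all of the change comes from the course, both would rest on the wrong component.

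**Working it through.** The plan gives no figure for the share of either component, so there is none to reproduce. The check has three parts.

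**1. Can the pre-post change be divided?** Let *a* be the app effect, *c* the course effect, *ac* any interaction, and *t* everything else that changes with time (maturation, regression to the mean). Then

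mean(T1 or T2) − mean(T0) = *a* + *c* + *ac* + *t*.

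Both components are off at T0 and on at T1 and T2 for every family. In a design matrix with columns for intercept, app and course, the last two columns are identical, so the rank is 2 of 3. A true state with *a* = δ and *c* = 0 gives the same expected data as one with *a* = 0 and *c* = δ. More participants or a different model would not change this.

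**2. Does the usage analysis get round it?** Usage differs between families, so a slope can be estimated, but course engagement differs too. With standardised variables, let the effect of app use be βa, the effect of course engagement βc, and their correlation r. A model with app use alone estimates

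slope = βa + βc × r.

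The documents give neither βc nor r. For scale only, assume βa = 0 and βc = 0.21 SD per SD. The value 0.21 is the planning effect size in the Sample size section, borrowed here as a convenient magnitude and not as an estimate of the course effect.

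| r (assumed) | app-use slope with no app effect |
|---|---|
| 0 | 0 |
| 0.3 | 0.21 × 0.3 = 0.063 |
| 0.5 | 0.21 × 0.5 = 0.105 |
| 0.7 | 0.21 × 0.7 = 0.147 |

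The covariates listed under the additional analyses are sociodemographic factors, co-sleeping and media use. None stands in for course engagement.

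**3. Does the stated caveat cover this?** The last limitations paragraph of the Discussion says that effect sizes are not causal, because changes may have causes besides the intervention. That concerns *t* in the first formula. It does not say that *a* and *c* are inseparable, and its final sentence goes on to efficacy of the app alone.

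**The case against.** The best defence is that the plan is more careful than this suggests. The governing efficacy aim is joint. Efficacy is secondary and called preliminary, the usage analysis is exploratory, and the Abstract already describes the usage question as one of association. If the effect of the whole package is not causal, neither is the share of one component. Parents also rate the app and the course separately, so the distinction is not ignored. All of this is true and makes the point milder. It does not remove it: parents' ratings do not identify separate effects, the general caveat leaves the inseparability unsaid, and objective 4 still speaks of the app affecting outcomes in order to issue advice. Which covariates enter an exploratory model is ordinary analysis-plan content, so their absence from the article is not counted as a fault.

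Three stronger readings are tempting, and the documents do not support them.

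- **The plan assigns child outcomes to the app and parenting stress to the course.** The hypothesis that "parenting stress will be significantly reduced 12 weeks after the start of the use of the email psychoeducational program" and its counterpart for the child outcomes set time points. The Introduction puts parental stress under the app, so there is no consistent split.
- **The sample size contradicts an app effect.** The section does say "For the parent training, we first considered effects on child outcomes as a basis for sample size calculation", but it names both components as considered. The value used, d = 0.21, comes from universal prevention programmes in general; the parent-training figure is 0.20. A borrowed planning value does not assume that the app adds nothing.
- **Course quizzes in the app would fill the usage levels.** The plan says only that "The knowledge learned can be tested weekly in a small quiz in the Aumio app". The quiz is thus optional, nothing says that an app opening counts as a use, and the feasibility outcome already gives audio content played as its example of usage.

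**Conclusion.** The point holds as one of interpretation. Under joint delivery in a single group, neither the T0–T1–T2 changes nor the usage slopes can be credited to the app, and four places in the article word them as if they could.

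The non-separability of the pre-post changes follows from the design and needs no assumption. Its numerical consequence is unknown: the app's share could be anything from none to all of the change. The slopes of 0.06 to 0.15 SD rest on an assumed absence of any app effect, an assumed course-engagement effect of 0.21 SD per SD and assumed correlations of 0.3 to 0.7. They show what could happen, not what will.

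The required sample size is not affected. Nor does the point show that the app is ineffective or that the single-group design is unsuitable for a feasibility study.

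**What to change.** 1. **Wording.** In the last paragraph of the Introduction, in objective 4 and in the last limitations paragraph of the Discussion, describe T0–T1–T2 changes as changes under the combined package. Describe usage results as associations, as the Abstract does. Add one sentence to the limitations: effects of the app and of the course cannot be separated in this design.
2. **Usage analysis.** Take audio content played, already named under the feasibility outcome, as the measure of app use. Report the app-use slope with and without the weekly quiz measure of course engagement, which is already collected.

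The second step is a sensitivity check and does not identify an app effect. The quiz is optional and records answers given, not e-mails read or advice followed. If it measures course engagement with reliability ρ and purely random error, the spurious part of the slope falls from βc × r to βc × r × (1 − ρ) / (1 − ρr²), which is zero only when ρ = 1. Because the quiz sits inside the app, its errors may also be related to app use, and the adjustment could then err in either direction.

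**Cost.** No new participants or data are needed: a few sentences, one model term and a filter on logged events. Claims become narrower, and the adjusted slope is less precise. If app use and the quiz measure correlate at 0.3, 0.5 or 0.7, the slope's variance is multiplied by 1 / (1 − r²) = 1.10, 1.33 or 1.96, before any gain from smaller residual variance.
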